To date, there is no research looking at the efficacy of psychological therapy to treat mental health issues delivered by video consulting to adults with a moderate to severe TBI. The purpose of this paper is to describe the design of a non-inferiority, randomized controlled trial, to examine whether an eHealth-based delivery of the ACT-Adjust treatment program achieves the same treatment effects as face-to-face delivery. It also will examine the efficacy of ACT-Adjust when compared to a wait-list control group and determine whether treatment gains are sustained three months after the intervention.

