**Figure 1 F1:**
[figure not shown]
Study flow diagram.

This paper describes the study protocol (Dated September 30, 2019; Protocol Version 1.0) to comply with the Standard Protocol Items: Recommendations for Interventional Trials (SPIRIT) (Chan et al., 2013), see Supplementary Table 1 for Spirit Checklist. The trial will be conducted according to the Consolidated Standards of Reporting Trials (CONSORT) of Electronic and Mobile HEalth Applications and onLine TeleHealth (CONSORT E-HEALTH) statement (Eysenbach, 2011), CONSORT Social and Psychological Interventions (CONSORT-SPI) (Montgomery et al., 2018) guidelines and CONSORT extension for the reporting of non-inferiority trials (Piaggio et al., 2012). The trial has been registered on the Australian New Zealand Clinical Trials Registry (ANZCTRN2619001602112). Refer to Appendix I for more details.

The study will commence immediately following ethics approval and recruitment of participants will continue for ~2 years. The overall duration of the study will be 3 years to allow for those in the wait list control condition to complete the intervention and the follow up assessment, and for data analysis and dissemination of results. To test the efficacy of the intervention, the study will test the following hypotheses:

ACT-Adjust intervention: Participants in the active treatment regardless of delivery (FtF vs. VC) will demonstrate increased psychological flexibility and decreased psychological distress following the intervention, compared to those in the control group (waitlist).eHealth: There will be no differences in primary and secondary outcomes between participants who receive the ACT-Adjust intervention by FtF compared to those who receive it via VC.Sustained treatment effects: Participants in the active treatment condition, ACT-Adjust (VC and FtF), will maintain their gains three months post intervention.

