### Randomization

The randomization process was performed by a researcher independent of the research team. A computer generated randomization list was generated for each phase of the study using online randomization software, Sealed Envelope (Sealed Envelope Ltd, 2019). The initial randomization had a ratio of 2:3:2 (FtF:WL:VC), with a permuted block size of seven. Following Time 2 Data Collection (13 weeks after Baseline/Time 1), wait list control participants will be randomized to the ACT-Adjust intervention on a ratio of 1:1 (FtF:VC), using a permuted block size of four. The results for both phases were placed in sequentially numbered opaque and sealed envelopes. Following completion of a participant's baseline assessment, the Research Assistant will open the next sequential randomized envelope available to determine the participant's assigned condition. The following allocations are required: ACT-Adjust face-to-face *n* = 16 participants; ACT-Adjust eHealth *n* = 16 participants; Waitlist control *n* = 24 participants.

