The shortened session times (~60 min) is proposed to assist in reducing fatigue and improving attentional processes for participants with cognitive impairments. The additional relapse prevention session (Session 9), aims to improve sustainability of treatment gains which were not achieved in the original ACT-Adjust clinical trial (Whiting et al., 2020). Metaphors were substituted to be VC compatible and more concrete (e.g., Chinese Finger Trap) enhancing participants' comprehension of the session focus. Further strategies to compensate for participants' cognitive impairments and fatigue after TBI translated from the original ACT-Adjust trial, included reviewing and repeating session material at the beginning of the following session, and provision of a hardcopy of the participant workbook printed in size 14 font, with a Flesch Readability Ease rating of 76.4 and Flesch-Kincaid Grade Level of 4.8. In addition, the therapist facilitates completion of workbook exercises, and session specific text message reminders are provided to facilitate completion of between-session home tasks, and for fatigue management, sessions were scheduled at a time favored by the participant, breaks were provided if required and sessions rescheduled if participants felt unable to attend. A summary of the program content is available in Table 1. The intervention will be delivered throughout New South Wales, Australia, by authors DW, MM, and JW and other trained mental health professionals recruited to the project, using the ACT-Adjust 2.0 Therapist Manual.

**Table 1 T1:** Summary of the ACT-Adjust 2.0 program.

**Session no**.	**Content**
1	**Confronting the Agenda** Introduction to the program—Guidelines and boundaries, reasons to see the psychologist, aims of ACT-Adjust, program outline Administer measures Exercise: Mindfulness activity (Mindfulness of the breath, 2 min) Confronting the agenda—identifying individual issues, workability, breathing, mindfulness exercise Home task—Introduce concept of home tasks, reasons for home tasks and home task contract, home task rating sheet Conclusion—Brief summary of the session

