### Data Analysis

Data will be entered into SPSS statistics software (IBM Corp, 2019), reviewed for missing data and then screened for normality on all outcome measures and for each treatment group. Prior to the main analysis, between groups comparisons will be undertaken to test for equivalency of the groups using chi-square and *t*-tests. Where participants withdraw or are not contactable for the follow up assessment, the last recorded measures will be carried forward to remaining assessment points for data analysis. Primary analysis will be implemented on an Intention-to-Treat basis, using hierarchical linear mixed models to study the differential effects of each treatment condition. For the post-treatment analyses between the three treatment conditions, analysis will focus on linear time effects, treatment conditions and interactions. Cohen's effect size will be calculated for all analyses. Analyses will focus on the estimated mean differences relative to pre-treatment levels on primary and secondary outcome measures (see Table 3). For the longer-term treatment effects, the non-inferiority of the face-to-face and video consulting will be assessed at the 3-month follow-up.

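### The one analysis named for the 3-month follow-up compares the two delivery modes, so it cannot test whether gains are maintained (Hypothesis 3)

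*Protocol article*

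**What the plan says.** The Overview of Study Design and Research Hypotheses sets three hypotheses: active treatment against waitlist, no difference between face-to-face (FtF) and video (VC), and durability. The third says that participants in ACT-Adjust, VC and FtF together, "will maintain their gains three months post intervention". The Introduction gives the same aim, to "determine whether treatment gains are sustained three months after the intervention". The description of ACT-Adjust 2.0 explains the interest: the added Session 9 "aims to improve sustainability of treatment gains which were not achieved in the original ACT-Adjust clinical trial".

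The Data Analysis section then divides the work by time. For the end of treatment: "For the post-treatment analyses between the three treatment conditions, analysis will focus on linear time effects, treatment conditions and interactions". For the later time: "For the longer-term treatment effects, the non-inferiority of the face-to-face and video consulting will be assessed at the 3-month follow-up". A further sentence, tied to no visit, reads "Analyses will focus on the estimated mean differences relative to pre-treatment levels on primary and secondary outcome measures (see Table 3"). For participants who withdraw or cannot be reached, "the last recorded measures will be carried forward to remaining assessment points for data analysis".

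**The concern.** Hypothesis 3 is about change within treated participants after therapy ends. The analysis attached to longer-term effects is about the gap between two treated groups at one visit. These are different quantities, and the second carries no information about the first.

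No untreated arm remains at 3 months to reveal a common decline, because waitlist participants are randomized to FtF or VC after Time 2. Relapse is also a realistic prospect, since the protocol itself says that the earlier trial did not sustain its gains. A conclusion of VC non-inferior to FtF at 3 months could therefore be read as support for durability when it gives none.

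**Working it through.** **The plan's own figure.** The only sample-size figure is 56, for a pre-to-post interaction on the AAQ-ABI (partial η² = 0.17, power 0.80). With α assumed to be 0.05, a three-group, two-time interaction needs 51 or 53, depending on the noncentrality convention. Rounded up to whole blocks of seven, either gives 56. The figure is plausible, but it does not concern the 3-month visit, and nothing below rests on it.

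**Step 1: the two targets.** Write g for the gain at end of therapy and r for the share retained at 3 months, equal in both modes.

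- Hypothesis 3 concerns mean T3 minus mean T2 in treated participants: rg − g = −(1 − r)g.
- The named test concerns VC minus FtF at T3: rg − rg = 0 for every r.

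The share retained drops out of the second quantity.

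**Step 2: chance of passing non-inferiority.** This was simulated with a two-sample t-test, one-sided 0.025, 40,000 runs and SD 1. The gain was set at 0.9 SD: f = √(0.17/0.83) = 0.453 and d = 2f = 0.905, if two equal groups are assumed. The article states neither α nor a margin, so both are assumptions. The 28 per arm is 16 plus half of the 24 waitlist participants.

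| n per arm | margin (SD) | 100% kept | 50% kept | 0% kept |
|---|---|---|---|---|
| 16 | 0.50 | 0.277 | 0.278 | 0.276 |
| 16 | 0.75 | 0.541 | 0.537 | 0.537 |
| 16 | 1.00 | 0.779 | 0.781 | 0.780 |
| 28 | 0.50 | 0.449 | 0.455 | 0.454 |
| 28 | 0.75 | 0.786 | 0.786 | 0.787 |
| 28 | 1.00 | 0.958 | 0.958 | 0.956 |

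Differences along a row are simulation noise. By Step 1 the equality holds for any gain, SD or margin.

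**Step 3: what a change from baseline would show.** T3 minus T1 equals rg. At r = 0 it is zero, so full relapse is visible. At r = 0.5 and g = 0.9 it is 0.45 SD, still an improvement on baseline although half the gain has gone.

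**Step 4: carry-forward.** For a participant last seen at T2, T3 is set equal to T2, so the recorded loss is 0. If a share p is carried forward and the others are typical, the estimated loss is (1 − p) times the true loss. No dropout rate is stated. With p = 20% as an assumption, the loss shrinks by a fifth, and a complete relapse would appear as 20% retention.

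**Step 5: precision of a direct estimate.** The half-width is t(0.975, n − 1) × √(2(1 − ρ)) / √n in SD units, with equal SDs at T2 and T3 and no attrition. The correlation ρ is assumed.

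- n = 32 (16 + 16), t = 2.040: 0.32 at ρ = 0.6, 0.28 at 0.7, 0.23 at 0.8.
- n = 56 (adding the 24 treated waitlist participants), t = 2.004: 0.24, 0.21 and 0.17.

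**The case against.** The best reply is that the non-inferiority test is not the whole of the 3-month analysis. The sentence on differences from pre-treatment levels is not limited to the end of therapy, and the Table 3 it cites schedules every primary and secondary outcome at T3 and T4. Appendix I also lists 3 months in the timeframe of the primary outcomes. On a fair reading, a baseline-to-3-month change would be estimated. This stands. A reader might infer that the trial has no other 3-month analysis and could hide a return to baseline in both arms. The documents do not support that, because such a change would expose full relapse.

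A second reply is that the exact contrast and the criterion for maintenance are ordinary content of an analysis plan that is not shown. That is partly right, and silence alone would be no finding. But the article is not silent: it opens the sentence with longer-term effects and attaches a comparison that cannot address their maintenance.

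A reader might also assume that the trial will declare maintenance from a non-significant T2-to-T3 loss, and compute how often that would mislead. At ρ = 0.7 such a rule misses a 0.3 SD loss 43% of the time with 32 participants and about 19% with 56. The protocol contains no such rule, so these figures do not measure a fault in it.

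Finally, carry-forward affects other analyses too. It is raised here only because it pushes directly towards Hypothesis 3.

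**Conclusion.** The point holds in a limited form. The only analysis named for the 3-month visit addresses Hypothesis 2, and its chance of success is unrelated to whether gains are kept. This follows from algebra and needs no assumption about margin, SD or effect size. A baseline-to-3-month change, if the general sentence is meant to cover it, would reveal full relapse but does not test loss after the end of therapy. Carry-forward removes that loss for anyone missing after T2. Hypothesis 3, a stated aim and a reason for redesigning the programme, is therefore left without an analysis that tests it. The sizes in Steps 4 and 5 depend on the assumed dropout and correlations; the mismatch does not.

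**What to change.** Add a separate analysis for Hypothesis 3:

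- From the mixed model, with time as a categorical factor, estimate the pooled ACT-Adjust (FtF + VC) change from end of therapy to 3 months, alongside the change from baseline to 3 months, each with a 95% CI.
- Use observed scores only, with none carried forward.
- Include treated waitlist participants through their own post-therapy and 3-month visits, and say which pre-therapy score is their baseline.
- Claim maintenance only if the interval excludes a loss beyond a retention limit that the investigators state in advance.
- Keep the VC versus FtF non-inferiority test as the analysis of Hypothesis 2.

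The visits and measures are already scheduled, so only analysis wording changes. The cost is that maintenance becomes harder to claim. For illustration, with no true loss, loss limits of 0.3 to 0.5 SD and correlations of 0.5 to 0.7, the power of such a test (one-sided 0.025) runs from 0.38 to 0.94 with 32 participants and from 0.60 to 0.997 with 56, before attrition. Those limits are examples; the choice belongs to the investigators.

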## Discussion

Results from this project will have implications for how barriers to psychological treatment access can be overcome amongst individuals with a TBI, living in remote and regional areas of Australia. Improved accessibility will be provided to these individuals by psychologists appropriately trained in using evidence-based psychological treatment. Furthermore, it will extend the current evidence base of the ACT-Adjust psychological treatment of mental health issues in individuals with a TBI. Finally, it will also have implications for telepsychology, that is, psychological treatments delivered by video consulting.

The trial aims to address mental health issues for individuals with a moderate to severe TBI living across all areas of NSW, Australia with the aim of improving overall quality of life by reducing psychological distress and increasing psychological flexibility. This project is significant since it is the first phase II trial that tests the efficacy of an ACT program for civilians and the first trial using an eHealth modality (telepsychology by VC) with clients experiencing a TBI. The project will (i) contribute to the evidence base for Acceptance and Commitment Therapy (ACT), eHealth and treatment of mental health issues after a TBI, and (ii) assist in addressing access to psychological therapy for individuals who may have difficulty seeing a psychologist face to face due to geographical location or transportation limitations.

### Potential Strengths of the Study

The study has been designed to meet the CONSORT guidelines for non-inferiority trials, psychosocial interventions and eHealth delivery (Eysenbach, 2011; Piaggio et al., 2012; Montgomery et al., 2018). It builds on a previously published RCT using an adaptation of the ACT-Adjust program which indicated statistically and clinically significant reductions in depression and stress but with a smaller sample size (Whiting et al., 2020). The project is a multi-site study to enable recruitment across a wide geographical area and will recruit individuals living across the state of NSW, Australia. The ACT-Adjust intervention will be delivered by clinicians (e.g. clinical psychologists, social workers, etc.) with experience in both ACT and TBI.

### Potential Limitations of the Study

There are some potential limitations in the generalizability of findings to use of eHealth in wider clinical practice contexts. Specifically, this research supplies participants with equipment and internet data to ensure efficient and seamless telepsychology sessions are delivered by VC. Also, participants will be trained by the Research Assistant in using the VC platform prior to commencing treatment. This level of service is unlikely to be achieved in general clinical practice where clinicians will have to use existing client knowledge and resources including both software and hardware. The study is also limited to English speaking participants and those without current comorbid psychiatric symptoms, therefore there is limited generalizability to other culturally and linguistically diverse groups as well as to individuals with comorbidities.

This study meets the gold standard of clinical trial delivery to provide additional evidence of ACT with individuals who have a TBI. It will also contribute to the research base on feasibility and effectiveness of eHealth for people with TBI.

## Ethics and Dissemination

### Ethical Considerations

Ethical approval for the study was granted by the South Western Sydney Local Health District Human Research Ethics Committee (2019/ETH13152), and local site specific assessments were authorized across trial sites (Liverpool Brain Injury Rehabilitation Unit: 2019/STE16924; Bathurst Health Service: 2019/STE17981; Illawarra Brain Injury Service: 2019/STE17982). Any protocol amendments will be reviewed by the steering committee and then be submitted for approval to the relevant ethics committee, for example, the addition of more recruitment sites. These amendments will also be submitted for approval to the clinical trial registry, ANZCTR.

Confidentiality for participants will be ensured as all measures administered will be deidentified using a unique identifier. The unique identifier will be linked to the participant's name and this personal information stored separately in a password protected spreadsheet located on a secure server at SWSLHD, accessed by only the co-ordinating Chief Investigator (DW) and Research Assistant (SC). Consent forms (paper versions) will be stored separately from measures administered (see below for data storage).

Any incidents of harm will be recorded in a secure file and ongoing management of participants will be undertaken by the psychologist delivering the intervention who will record participants' weekly distress using a self-report measure (DASS-21). In addition, a suicide risk assessment is included in the treatment protocol in the first week of treatment. Some participants will be undertaking other rehabilitation treatment and all participants will have a nominated treating doctor to provide additional support. Participants will be given phone numbers and contact details of support systems between sessions. This will ensure adequate monitoring of participants will occur during the trial. Post-trial care will be maintained by the rehabilitation team at the BIRP or icare treatment team. It is not anticipated any harm will occur from participants receiving this treatment, as both clinical and statistically significant improvements in mood were achieved when the intervention was delivered in previous research (Whiting et al., 2020).

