### Treatment Conditions

All participants will receive their intervention in conjunction with constrained usual care (Freedland et al., 2011). Usual care may involve prescribed components of multidisciplinary interventions (e.g., social work, physiotherapy, occupational therapy, case management, speech therapy, diversional therapy, and/or vocational assistance) except for clinical psychology, as well as regular medical reviews by a rehabilitation physician and/or general practitioner. Participants who persistently report extremely high levels of psychological distress (DASS-21 subscales in the extremely severe range, as measured at the beginning of each session) or express suicidal intent during therapy, will be removed from the study and offered immediate psychological treatment. In addition, the treating clinician will assess participants' ability to attend to the session material whether from cognitive impairment or fatigue and make necessary treatment adjustments with regard to rest breaks and/or rescheduling sessions.

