#### Wait List Control Condition

The wait list control group will receive constrained usual care as discussed above excluding clinical psychology. They will be engaged in their prescribed rehabilitation activities for a period of 13 weeks and then complete the Time 2 assessment (post), at which stage they will be randomized to receive either ACT-Adjust FtF or via VC.

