Each participant enrolled in the trial will receive a Therapy Kit comprising a hardcopy of the ACT-Adjust 2.0 Client Workbook and individually wrapped materials for Session 2 (Chinese finger trap), Session 5 (packet of sultanas), and Session 6 (values card pack). All participants will complete the ACT-Adjust 2.0 program (Table 1), which is comprised of 9 × 1.5 h sessions. The week prior to commencing the program (and before randomization occurs), participants will meet with the treating psychologist in person to complete Baseline assessments. Sessions 1–7 will occur on a weekly basis, and a 2-week break will be placed between Sessions 7 and 8, and a 4-week break between Sessions 8 and 9. If required, sessions may be rescheduled by arrangement between the participant and treating psychologist, and will be rescheduled as soon after the original session as is feasible. Following the completion of Session 9, participants will meet with an independent blinded assessor to complete the Time 2 assessment measures (within 1 week of treatment completions). Three months after completing Session 9, participants will meet again with an independent blinded assessor to complete Time 3 assessment measures.

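### The stated suicide-risk assessment and suicidal-intent rule start with treatment, so the 24 of 56 wait-list participants reach them only after a 13-week wait, although a psychologist sees everyone before randomization

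*Protocol article*

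**What the plan says.** Two provisions deal with suicide risk, and the article ties both to treatment.

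- **Assessment.** Ethical Considerations states that "a suicide risk assessment is included in the treatment protocol in the first week of treatment". The same section gives ongoing management and the weekly DASS-21 to the psychologist who delivers the intervention.
- **Escalation rule.** Treatment Conditions covers two groups: "Participants who persistently report extremely high levels of psychological distress", judged on the DASS-21 taken at the start of each session, and those who "or express suicidal intent during therapy, will be removed from the study and offered immediate psychological treatment".

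The wait-list arm is described separately. Under Wait List Control Condition, "The wait list control group will receive constrained usual care as discussed above excluding clinical psychology". This lasts 13 weeks, up to the T2 assessment. Only then are these participants randomized to one of the two forms of ACT-Adjust.

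Before any allocation there is a visit common to all arms. Under Intervention: ACT-Adjust 2.0, "The week prior to commencing the program (and before randomization occurs), participants will meet with the treating psychologist in person to complete Baseline assessments". According to Randomization, once that assessment is complete, "the Research Assistant will open the next sequential randomized envelope available to determine the participant's assigned condition".

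**The concern.** Entry requires clinically significant distress on the DASS-21, and people already receiving a psychological intervention are excluded. Those allocated to wait then have usual care without clinical psychology. They are also the participants for whom the trial's own risk assessment and its rule for acting on suicidal intent do not operate until the wait is over. The protocol itself treats suicidal intent as a reason for immediate treatment, and that standard should not depend on the arm drawn from the envelope.

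What is at stake is patient safety. On the stated sequence, a person with suicidal intent could be allocated to wait before the trial's assessment is made, even though a psychologist has just met that person face to face.

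**Working it through.** **1. Arm sizes.** The total is 56 (Sample Size and Power Calculations) and the ratio is 2:3:2 for face-to-face, wait list and video (Randomization).

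- Face-to-face: 56 × 2/7 = 16
- Wait list: 56 × 3/7 = 24
- Video: 56 × 2/7 = 16

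These match the stated allocations. The wait-list share is 24/56 = 42.9%. The two active arms together are 32/56 = 57.1%.

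**2. When each provision first applies, on the stated text.**

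| Provision | Active arms (32) | Wait list (24) |
|---|---|---|
| In-person baseline with a psychologist, before allocation | Yes | Yes |
| Suicide-risk assessment | First week of treatment | First week of treatment, which comes after T2 |
| Extreme-distress trigger (session DASS-21) | From the first session | From the first session, after T2 |
| Suicidal-intent trigger | Once therapy starts | Once therapy starts, after T2 |
| Weekly DASS-21 by the treating psychologist | During treatment | None until treatment, after T2 |

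T2 for the wait list falls 13 weeks after baseline, so the delay for these 24 people is at least 13 weeks.

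**3. Effect of moving the assessment to baseline.** Stated early coverage is 32 of 56 (57.1%), in the first week of treatment. With the assessment at the baseline visit it becomes 56 of 56, all before allocation. The gain is 56 − 32 = 24 people, each assessed at least 13 weeks sooner.

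**4. Recruitment cost.** The article projects screening from an earlier trial that screened 90 people to enrol 17: 90/17 = 5.29 screened per participant. Then 56 × 90/17 = 296.5, which reproduces the stated figure of about 297. Each person referred at baseline and replaced therefore costs about 5.3 more screened.

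The article gives no rate of suicidal intent. Purely as an assumption, 1 to 3 such people would mean:

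- 1 × 5.29 = 5.3 more screened (about 2% of 297)
- 3 × 5.29 = 15.9 more screened (about 5% of 297)

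**The case against.** The strongest reply is that the article describes a check within the treatment manual and never says it is the only one. Procedures for risk found at consent, baseline or outcome visits are often left to the full protocol and the ethics application. This stands as a limit. A reader might infer that no suicide-risk check exists at baseline and cite Table 3, which lists none. The document does not support that inference: Table 3 also omits the first-week assessment that the article says takes place, and the Goal Attainment Scale used in the later sessions. Its silence is not evidence either way. The point rests only on where the text places the provisions it does state.

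A second reply is that the wait list is not unprotected, and this is also correct. Every participant has a nominated treating doctor. Usual care may include case management and social work, "as well as regular medical reviews by a rehabilitation physician and/or general practitioner". Severe psychiatric illness is excluded, and the DASS-21 is taken at baseline by a psychologist. Support contacts are given too, although the wording places them between sessions. It would be wrong to read the point as saying these 24 people have no safety net. What remains is that none of these is a stated suicide-risk assessment or a stated trigger for escalation, so they do not replace the two provisions in question.

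A third reply is that 24 of 56 is only the size of the arm, and that a baseline check cannot detect risk that emerges later in the wait. Both parts stand. The figure is not a risk estimate, and the change proposed here does not add monitoring inside the 13 weeks.

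**Conclusion.** The concern holds in this limited form. As stated, the trial's suicide-risk assessment and its escalation rule reach 24 of 56 participants (42.9%) only after at least 13 weeks without clinical psychology, while an in-person psychologist visit before randomization could have covered all 56. General safeguards reduce the exposure but do not supply the missing assessment or trigger.

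The conclusion assumes that the article's placement of the two provisions reflects the full protocol, which may contain further steps; confidence is therefore moderate. The number of people who would be identified cannot be estimated from the document. The matter deserves correction because it concerns safety and the remedy uses a visit that already exists.

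**What to change.** 1. Carry out the existing suicide-risk assessment for every participant at the in-person baseline visit, before the envelope is opened. Keep the check in the first week of treatment.
2. Do not randomize anyone with suicidal intent at baseline. Offer immediate psychological treatment; the person stays unrandomized whether or not the offer is accepted. This settles the case of someone who declines, whom the exclusion for current psychological treatment would not catch.
3. Let intent disclosed at T2 or T3 prompt a safety referral in any arm. The blinded assessor can raise it without being told the arm. Keep these participants' outcome data in the intention-to-treat analysis.

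**Cost.** A protocol amendment, a slightly longer baseline visit with staff already present, and a presumably small but unquantified number of replacements at about 5.3 screened each. A participant in an active arm who is referred at T2 and takes up outside treatment would carry it into the 3-month comparison of face-to-face and video delivery; this affects only those who disclose intent. Whether to add a check during the 13-week wait is a separate decision for the sponsor and ethics committee.
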